## Abstract

**Background:**

Cancer remains an escalating and challenging public health issue. The management, especially palliative care (PC), is disintegrated and out of reach of in need patients. The overall aim of the project is to develop a feasible and scalable Comprehensive Coordinated Community based PC model for Cancer Patients (C3PaC); congruent with socio-cultural, context and unmet needs in north India.

**Methods:**

A mixed method approach will be used for three-phased pre- and post-intervention study in one of the districts of North India, having a high incidence of cancer. During phase I, validated tools will be used for quantitative assessment of palliative needs among cancer patients and their caregivers. Barriers and challenges for provision of palliative care will be explored using in-depth interviews and focus group discussions among participants and health care workers. The findings of phase I along with inputs from national experts and literature review will provide inputs for the development of the C3PAC model in phase II. During phase III C3PAC model will be deployed over a period of 12 months and its impact assessed. Categorical and continuous variables will be depicted as frequency (percentages) and mean ± SD/median (IQR) respectively. Chi-square test/Fischer test, independent samples Student t-tests and Mann–Whitney U tests will be used for categorical, normally and non-normally distributed continuous variables, respectively. Qualitative data will be analyzed using thematic analysis using Atlas.ti 8 software.

**Discussion:**

The proposed model is designed to address the unmet palliative care needs, to empower community-based healthcare providers in comprehensive home-based PC and to improve the quality of life of cancer patients and caregivers. This model will provide pragmatic scalable solutions in comparable health systems particularly in low- and lower-middle Income countries.

**Trial registration:**

The study has been registered with the Clinical Trial Registry-India (CTRI/2023/04/051357).

## Background

With an estimated cancer prevalence of 2.5 million, and the majority presenting in advanced stages, more than 1 million people need palliative care (PC) in India [1]. Most of these patients present in advanced stages of cancer due to poverty, lack of awareness, poor health-seeking behaviour, and scarcity of cancer diagnostic and therapeutic facilities [2]. Although access to PC is essential to achieve universal health coverage, very few (< 4%) Indians have access to it. This gap exists despite the ongoing National Programme for Prevention and Control of Cancer, Diabetes, CVD and Stroke (NPCDCS) and National Programme for Palliative Care (NPPC) [3]. The lack of healthcare facilities and trained workforce in providing PC make the situation abysmally bad in rural low-to-middle income countries (LMIC) [4, 5]. With 70% of our population residing in rural India with poor access to healthcare services, there is a long-felt need for community-based PC [6]. Community-based PC has been shown to be the least expensive and most cost-effective delivery model [7, 8]. Despite its vast demography and geography, and a huge burden of non-communicable diseases, India has only a handful of community-based PC services. Kerala, the southernmost state of India, alone has about 90% of approximately 1000 PC services in India [9, 10]. Lack of access to quality PC is therefore the norm rather than the exception; ranking India poorly (59th out of 80 countries) in the quality of death index [11]. Most of Kerala’s success can be attributed to the network of community initiatives known as ‘‘Neighbourhood Network in Palliative Care (NNPC)’’ which is the largest community-owned PC service in the world [12]. Various socio-cultural factors (charity, collective efforts, Panapayatt or money exchange, high literacy rate, local self-help groups, community ownership, micro fundraising) responsible for the success of NNPC in Kerala are different in other parts of India (like philanthropic services offered by gurudwaras in the Malwa Region), necessitating PC delivery models congruent with their specific cultural, socioeconomic, disease, demographic, and need differences [13]. The gap in service delivery is well reflected in the joint statement by the Indian Association of Palliative Care and the Academy of Family Physicians of India which in 2018 proposed an urgent need for nationwide community-based PC programs [14]. Lack of healthcare professionals (HCP) training in PC is one of the common reasons for HCP resistance to and poor availability of PC in developing countries [15]. Investment of time and resources in PC training is a recommended facilitator in addressing the shortage of PC workforce ubiquitous in LMICs like India [16]. This exorbitant need- supply mismatch demands development of models targeting both local socio-cultural barriers and PC needs. In order to address this gap, this project has been planned in Bathinda, Punjab, a district in the “Malwa region” with a well-documented high incidence rate of cancer [17, 18].

## Aim

The overall aim of the project is to develop a feasible and scalable Comprehensive CoordinatedCommunity basedPalliative Care model for Cancer Patients (C3PaC) congruent with the socio-cultural diversity and unmet needs unique to the population of interest.

## Methods/design

To achieve this aim, a three-phased strategy is planned, each addressing a specific research question and objective (Fig. 1).

**Fig. 1 Fig1:**
[figure not shown]
Phase-wise research questions and Objectives

### Study design and setting

This mixed-methods study will be undertaken by the All India Institute of Medical Sciences (AIIMS Bathinda), a tertiary care institute of national importance in northern India. The study will be implemented in one of the six-blocks (Goniana) of district Bathinda with an estimated population of 2,09,650 (as per the latest district administration report) (Fig. 2). The study area has been selected based on purposive sampling. The study will have following three phases (Fig. 3).

**Fig. 2 Fig2:**
[figure not shown]
Geographical location of the study site and setting

**Fig. 3 Fig3:**
[figure not shown]
Infographic depicting Project phases

### Phase I (need assessment/gap analysis)

A cross-sectional study with mixed-method design will be adopted. Following activities will be carried out in this phase:

#### Community sensitization workshops

Lack of awareness and knowledge is one of the key factors for suboptimal accessibility to PC [19]. Community sensitization workshops will be held with key stakeholders to orient them about the study and the need and importance of PC [1]. The stakeholders will include panchayati raj institutions (village sarpanch), community health workers like Accredited Social Health Activists (ASHA) and Auxillary Nurse Midwife (ANM), medical officers at the Primary Health Care Centre, medical specialists, and non-communicable diseases (NCD) cell In-charge at the Community Health Care Centre, district program officer of National Programme for Prevention of Cancer, Diabetes, Cardiovascular Diseases and Stroke (NPCDCS), voluntary organizations working in the field of cancer, private providers, and cancer patients. Permission from the concerned authorities will be duly obtained.

#### Key informant interviews

In-depth interviews (IDI)/focus group discussions (FGD) with stakeholders will be conducted to explore the PC needs, barriers and challenges. The interviews will be done using an IDI guide or FGD guide that will be developed in consultation with experts in PC, community medicine, and literature review. About 3 FGDs will be conducted among ASHA workers (tentatively 8 per FGD) and in-depth interviews will be conducted till saturation of data is achieved in other key informant interviews. We will tentatively interview 15–20 patients and their caregivers, 15–20 healthcare providers and 5–7 members of voluntary organizations through purposive and convenience sampling. Adult (18 years or more) patients with diagnosed cancer and their family members involved in patient care will be eligible for the interviews.

#### Door-to-door survey

This will be done by the project staff to identify cancer patients in the community. This exercise will be conducted with the help of ASHA workers. Structured need assessment tools (SPARC-45) and Supportive and Palliative Care Indicators Tool) will be used to allow structured assessment of the PC needs of the identified patients and their families. The supportive and palliative care indicators tool (SPICT) will be used for initial screening followed by the Sheffield profile for assessment and referral to care (SPARC-45). SPARC-45 has been chosen as it allows comprehensive assessment of needs encompassing various domains of PC in various settings [20, 21]. These tools will be adapted, translated into local language and validated for use in local settings after taking the permission.

#### Outcome of phase I

The expected outcome will be to identify the local epidemiology of cancer; symptom burden and experience; unmet needs of cancer patients (and their families) and barriers and challenges to accessing and providing PC. These findings will be helpful in the development of the proposed C3PaC model in phase II.

#### Phase II (development of model)

The C3PaC model will be developed based on the findings of the baseline assessment, expert consensus and literature review and will comprise of [5].

#### Structured training curriculum and training manual

This will be developed in consultation with the national experts (from the Indian Association of Palliative Care; All India Institute of Medical Sciences (AIIMS) New Delhi and AIIMS Bathinda and state and district program officers). Existing guidelines and training manuals in PC will be systematically reviewed and contextualized to the PC needs and training needs of the community health workers. Vernacular translation of the training manual in local languages (Hindi and Punjabi) will be done.

#### Training

The project staff along with the identified community health care personnel from the State Health Authorities, Punjab will be trained at the AIIMS Bathinda after taking permission from the concerned authorities. A multidisciplinary team of experts comprising palliative care specialists, community medicine experts, oncologists, medical social workers, nurses, and psychiatrists will impart comprehensive home-based PC training to potential patients and caregivers. Apart from didactic lectures, field-based experiential training will be provided. Pre- and post-training changes in the knowledge and attitude will be assessed using validated tools.

#### Liasoning within the community and referral pathway

A list of local voluntary organizations and non-governmental organizations (NGOs) working in the area of cancer, palliative care, education and vocational training will be formulated with the help of village heads (sarpanch), community health workers, and self-help groups of the area. Links will be established with these organizations and with cancer treatment centers providing comprehensive cancer-directed treatment to cater to the identified healthcare, physical, financial, and social needs. AIIMS Bathinda will also act as a referral center for patients in need of specialist palliative care services and cancer-directed treatment. Referral coordination, need-based longitudinal follow-up and simultaneous provision of PC will be done by the study team to ensure continuum of care.

### Phase III (deployment of the intervention and feasibility/impact assessment)

A quasi-experimental (pre-post design) will be adopted where the diagnosed patients in Phase I will be considered as controls. To these identified patients, the C3PaC model will be deployed in the form of an intervention over a period of 12 months. The focus will be to provide home-based PC to cancer patients throughout the cancer trajectory, with referral to a tertiary care center for either cancer-directed treatment or management of difficult-to-manage symptoms. The patient information (e.g. demographics, diagnosis, stage of cancer, treatment details, palliative performance scale; physical, psychosocial, and spiritual needs, follow-up details) will be keyed into an electronic record to enable electronic exchange of information among the team members [22].

After one year of intervention, post-intervention data collection will be done to assess the impact, feasibility, sustainability, and scalability of the model using a mixed-method approach. Validated tools like Quality of Life (QOL) version II and the European Organisation for Research and Treatment of cancer Quality of Life Questionnaire Core 30 (EORTC QLQ-C30) will be used after taking appropriate permissions to assess the impact of the C3PAC model on QOL pre and post-C3PAC model deployment. QoL version II has strategically been chosen as their validated translations in the local language are available and both have been used extensively in PC research; thereby improving the generalisability of the results [23–25].

To explore the feasibility and acceptability of this model, FGD and IDI will be conducted with the key informants (as Phase I). The sustainability of this model will be ensured by using the WHO Public Health Strategy for PC to strengthen health systems (Fig. 4) [1].

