#### Proposed Outcome of the study

The expected outcomes of the study are tabulated below (Table 1).

**Table 1 Tab1:** Expected outcomes of the study

Primary outcome	- Development of a feasible and sustainable Comprehensive Coordinated Community based Palliative Care model for Cancer Patients
Services	- % Cancer patients who received PC
Workforce capacity building	- Development of a structured training module for community-based PC. - Number of community health workers trained in PC
Monitoring indicators for evaluating impact of the model	- Change in HRQoL using EORTC QLQ-C30 pre and post C3PAC model deployment. (Permission to use the Hindi and Punjabi versions of EORTC QLQ-C30 has been obtained) - Change in symptoms as measured by an adapted symptom assessment scale. - % Cancer patients cared for at their preferred place of care

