## Discussion

Palliative Care interventions (like C3PaC) are inherently complex in that they are multi-component and multi-professional [26, 27]. To ensure their feasibility and cost-effectiveness; these interventions should be developed and tested systematically in phases starting with defining the components, barriers, and challenges to implementation (Phase I); developing the intervention (phase II) and implementation and assessing the effectiveness of intervention (Phase III) [26, 27].

The quality of PC services can be determined by how they address the unmet needs and to be met, they first need to be identified [28]. Need assessment (as in Phase I), inherent in the WHO definition of PC, helps in understanding the requirements of the target beneficiaries enabling them to maintain or improve the present state of well-being [29, 30]. It allows designing appropriate services to provide the right care to those “who” and “when” they need it. A systematic assessment of the quantum of target beneficiaries, their issues, sociocultural milieu, local means available, and existing barriers is essential to delineate the gaps, maximize resource utilization, and empirically plan and implement services [31].

Accustomed culture, lack of training, community awareness, and investment in PC are some of the biggest barriers to the provision of PC; necessitating addressing these barriers (training component of Phase II) to ensure sustainable PC services [20]. Poverty, lack of social security, and most healthcare expenditure being out of pocket in India, necessitate PC programs to cater to free medications, support children’s education, and alternative source of family livelihood (establishing links with voluntary organizations in Phase II) [32].

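### The Phase I patients called controls are the same people who then receive C3PaC, so the pre-post change cannot be read as the model's impact

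*Protocol article*

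**What the plan says.** The Phase III section of the protocol article defines the design: "A quasi-experimental (pre-post design) will be adopted where the diagnosed patients in Phase I will be considered as controls". It then names the recipients: "To these identified patients, the C3PaC model will be deployed in the form of an intervention over a period of 12 months". One later assessment is described: "After one year of intervention, post-intervention data collection will be done to assess the impact". Table 1 (Proposed Outcome of the study) lists "Change in HRQoL using EORTC QLQ-C30 pre and post C3PAC model deployment", together with change on an adapted symptom scale, among the indicators meant to show the model's impact.

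Under Study design and setting, "The study will be implemented in one of the six-blocks (Goniana) of district Bathinda". No comparison block, staggered start or other concurrent comparator is described.

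The Quantitative data section gives two sets of tests. Independent-samples tests are for comparisons between groups, which are not defined. A paired t-test or Wilcoxon test is for differences in mean scores. The abstract names only the independent-samples tests.

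**The concern.** A control shows what would have happened without the model. Here the controls and the recipients are the same people at two times, so the label promises something the design does not contain. Reading controls as own controls does not help, because a patient's earlier score does not show where that patient would have been a year later without C3PaC.

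Over 12 months in a cancer cohort, scores move for other reasons. Progression lowers them. Cancer treatment given in the same period can move them either way. If the sickest patients die or cannot respond, those left to be measured look better. The section on anticipated operational difficulties expects death and declining health, and plans for attrition, proxy measures and the timing of measures. It does not mention natural course.

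A fall could be read as failure although the model slowed a decline, and a rise as success although it did nothing. The article expects the results to be used in advocacy up to national level, so the wording of the conclusion matters.

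The label may also lead an analyst to treat pre and post scores as two independent groups.

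**Working it through.** The article states no sample size, power, standard deviation or effect size, so there is no figure of its own to reproduce. Everything below uses assumed inputs, and the missing sample size is not itself a criticism.

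**1. Bias.** Expected pre-post change = effect + drift. With no effect, the expected change equals the drift. With an effect of +0.2 SD and a drift of −0.2 SD, it is 0, and a real benefit is detected only 5% of the time.

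**2. False-positive rate with no effect.** Alpha is 0.05 (Quantitative data; two-sided assumed). Assume a within-patient correlation ρ of 0.6. In SD units, SE = √(2(1−ρ)/n), and P(p<0.05) = Φ(d/SE − 1.96) + Φ(−d/SE − 1.96) for drift d.

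| n | SE | d = 0.1 SD | d = 0.2 SD |
|---|---|---|---|
| 50 | √(0.8/50) = 0.126 | 12% | 35% |
| 100 | √(0.8/100) = 0.089 | 20% | 61% |
| 200 | √(0.8/200) = 0.063 | 35% | 89% |

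At n = 100 and d = 0.2, ρ = 0.5 gives SE 0.100, ratio 2.00 and 52%; ρ = 0.8 gives SE 0.063, ratio 3.16 and 89%. A larger sample makes the wrong conclusion more likely.

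On a points scale, with an assumed SD of change of 25 and n = 200, SE = 25/√200 = 1.77. A drift of 5 points gives 5/1.77 = 2.83, and p<0.05 about 81% of the time.

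**3. Independent-samples test on the same patients.** That test takes SE = √(2/n). The ratio to the paired SE is 1/√(1−0.6) = 1.58, so the standard error would be overstated by 58% at ρ = 0.6.

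**4. Regression to the mean.** If the worst fraction f on the baseline score enters, the mean shifts by (1−ρ)φ(c)/f SD, where c is the normal quantile of f. For ρ from 0.8 to 0.5:
- everyone enters: 0
- worst 70%: 0.10 to 0.25 SD
- worst half: 0.16 to 0.40 SD

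**5. What a second pre-deployment score can do.** Let Y0 be taken at the Phase I survey, Y1 just before deployment and Y2 after 12 months. The slope-difference contrast is (Y2−Y1) − k(Y1−Y0), with k = 12/gap in months. Under equal correlations, its variance relative to Y2−Y1 is [1 + (1+k)² + k²]/2:
- 12-month gap (k = 1): (1+4+1)/2 = 3
- 6-month gap (k = 2): (1+9+4)/2 = 7
- 3-month gap (k = 4): (1+25+16)/2 = 21

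To detect 0.3 SD with 80% power at ρ = 0.6, the paired n is (1.96+0.84)² × 0.8/0.09, about 70. This becomes 210 at a 12-month gap and 489 at a 6-month gap.

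Simulations with no true effect (SD 20, ρ = 0.6, 6-month gap) gave these mean apparent effects in points:

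| Scenario | Y2−Y0 | Y2−Y1 | Slope difference |
|---|---|---|---|
| Drift −8 per year | −12.0 | −8.0 | 0.0 |
| Worst half on Y0, no drift | +6.4 | 0.0 | −12.8 |
| Drift −8 per year plus a further −6 late | −18.0 | −14.0 | −6.0 |
| Drift −8 per year, half lost by a rule favouring better patients | −10.2 | −6.8 | −0.1 |

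The last row shows selective survival moving the simple change from −8.0 to −6.8. The slope difference stayed near zero there because each patient's slope was constant. It would give no such protection where dropout follows deterioration that begins after deployment.

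**The case against.** The article openly calls the design pre-post and quasi-experimental. Its primary outcome is development of a feasible and sustainable model, and QLQ-C30 change is a monitoring indicator. Assessment schedules are commonly left to the full protocol, so further measurements may exist. All of this stands, and it confines the harm to the impact claim. It does not supply a comparator, and the controls label is in the text.

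Three stronger readings are tempting but not supported.

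- **That regression to the mean inflates the result.** "The supportive and palliative care indicators tool (SPICT) will be used for initial screening" makes selection on poor status plausible. However, the Phase III section speaks of diagnosed patients and states no screening or score threshold for entry. Patients are found by a door-to-door survey. If all identified patients enter, the shift is 0.
- **That the interval before deployment is a true untreated own-control period.** Under the Phase II headings on training and on community links and referral, the article describes home-based care training that reaches patients and caregivers, referral coordination and provision of palliative care alongside. It does not say that these wait for deployment. Subtracting the change in that interval could remove part of the model's own effect.
- **That the article commits itself to an effectiveness conclusion.** The phrase "implementation and assessing the effectiveness of intervention (Phase III" sits in a general sentence on how complex interventions should be developed. The firmer ground is the wording about impact in the Phase III section and Table 1.

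The between-group tests may be meant for patient subgroups rather than for pre against post. The article does not say, which is a reason to state it.

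**Conclusion.** The point holds in this form: Phase III has no described control, the patients called controls are the recipients, and a pre-post change cannot be attributed to C3PaC. The bias equals whatever drift occurs and may run either way. On the assumed inputs (ρ = 0.6, drift 0.1 to 0.2 SD, n = 50 to 200), 12% to 89% of studies would show a significant change with no effect. These figures show how sensitive the test is to drift and do not predict this study's result. Regression to the mean adds to the bias only if entry depends on poor status.

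The correction should be made, since the main part needs only wording. It does not affect the primary outcome of developing the model.

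**What to change.** 1. In the Phase III section, replace controls with the same patients' own pre-deployment assessment, and state that there is no comparator.
2. State that change in quality of life and symptoms is analysed with the paired tests already listed under Quantitative data, not the independent-samples tests. Align the abstract.
3. Word conclusions as change associated with C3PaC, not impact or effectiveness. Name natural course, concurrent cancer treatment and selective survival as explanations that the design cannot exclude.
4. Optionally, give QLQ-C30 and the symptom scale both at the Phase I survey and just before deployment. Report the change between the two descriptively and take the main change from the later score. This removes regression to the mean from selection on the survey score, but not drift. The door-to-door survey names only SPICT and SPARC-45, and the article does not say when the existing pre score is taken, so one of the two occasions would be new.

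Do not make the slope-difference model the main analysis. Phase II activities may already reach patients, its variance is about 3 to 21 times larger for gaps of 12 to 3 months, it over-corrects if patients are selected on the survey score, and it does not in general remove accelerating decline or informative dropout.

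Cost: items 1 to 3 need only wording and lead to more modest claims. Item 4 adds one questionnaire round per patient.

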### Supervision of the study implementation

A project/policy advisory group (PAG) involving all key stakeholders will be formulated and apprised of the project activities through periodic meetings. The implementation plan will be continuously evolved with the inputs of the PAG. The activities will be periodically supervised and refined over the intervention period.

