Based on the principles of universal health care coverage, this study is planned to provide a continuum of care to cancer patients starting from detection, throughout the cancer trajectory, while receiving cancer-directed treatment and extending to end-of-life care. The research team has prior experience in establishing and functioning palliative care programs both at regional and national levels. Since PC provides the desired results when started early, preferably at the time of diagnosis, our model aims at timely initiation of care and integration of the model into the existing healthcare system, with an emphasis on primary care and community setting. Any public health interventions can be ethically challenged if activities cannot be sustained after the cessation of external funding [33]. A public health approach will be adopted to address sustainability throughout the planning, implementation, and evaluation of C3PaC (Fig. 4) [34, 35]. PC activities will be tagged alongside the existing community healthcare system to ensure ownership and continued program activities even after the cessation of the project [32].

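### Sustainability is part of the primary outcome, but the 12-month assessment can show only feasibility under project support and prospects for sustainability

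*Protocol article*

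**What the plan says.** Under Proposed Outcome of the study, Table 1 gives the primary outcome as "Development of a feasible and sustainable Comprehensive Coordinated Community based Palliative Care model for Cancer Patients".

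Phase III states that "the C3PaC model will be deployed in the form of an intervention over a period of 12 months", and then: "After one year of intervention, post-intervention data collection will be done to assess the impact, feasibility, sustainability, and scalability of the model". It adds that use of a WHO public health strategy will secure sustainability. The Phase III focus groups and interviews are given the purpose of exploring feasibility and acceptability.

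On who does the work, the section on community liaison and the referral pathway says: "Referral coordination, need-based longitudinal follow-up and simultaneous provision of PC will be done by the study team". The Training section says: "The project staff along with the identified community health care personnel from the State Health Authorities, Punjab will be trained". On oversight, the section on supervision says: "The activities will be periodically supervised and refined over the intervention period".

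The Discussion says what sustainability is for: "Any public health interventions can be ethically challenged if activities cannot be sustained after the cessation of external funding". It plans to attach palliative care activities to the existing community health system "to ensure ownership and continued program activities even after the cessation of the project".

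**The concern.** In the Discussion, sustainability is a property of the period after the project. The assessment in Phase III belongs to the period of the project. A service that stops when the study team leaves and one that carries on without it could give the same results at 12 months, so those results cannot distinguish the two.

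This matters because the word stands in the primary outcome and because of the use planned for the results. The section on sustainability and scalability foresees advocacy at district, state and national level, and the Strengths section foresees help to policy makers. A reader who is told that the model proved sustainable would take it that state services can run it without the study institute's team. The study as described would not have observed that.

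**Working it through.** The article gives no sample size, effect size or count on this point, so the check sets its statements side by side.

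1. **Claim.** The primary outcome contains two attributes, feasible and sustainable (Table 1). Phase III confirms that data will be collected to assess sustainability, so it is not only a design aspiration.
2. **Meaning.** The Discussion relates sustainability to two events, the end of external funding and the end of the project. Both lie after the deployment that is studied.
3. **Timing.** Deployment lasts 12 months and the assessment follows one year of intervention. Taking the assessment at about month 12, the observation described after withdrawal of support is 12 − 12 = 0 months. No later assessment and no interval without the team is described.
4. **Delivery during those 12 months.** The study team is assigned referral coordination, follow-up and provision of care. State personnel are trained with the project staff, and activities are to be attached to the existing system. The fair reading is shared delivery, in proportions that are not given. Activities are also supervised and refined throughout.
5. **Measures.** Table 1 lists the percentage of patients who received palliative care, a training module, the number of workers trained, change in quality of life, change in symptoms, and the percentage cared for in the preferred place. None of these as worded separates care given by the study team from care given by state workers. A patient cared for wholly by the study team counts fully in the first.
6. **Means of securing sustainability.** The WHO strategy, attachment to the existing system, stronger primary care and referral indicators for local providers are actions intended to bring it about. None is a measurement of whether it came about.

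Steps 2 and 3 settle the point: the claim concerns time after the project, and the described observation stops when the deployment does. Step 4 explains why the gap has content. If state workers carried everything unaided, the 12-month data would come close to the property claimed. With the study team carrying a share of unknown size, they do not.

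**The case against.** The strongest reply is that the primary outcome is the development of a model, with sustainability as a design attribute. On this view the remark about the end of funding is an ethical rationale and not an operational definition, and a mixed-method assessment can reasonably collect stakeholders' views on sustainability at 12 months. Part of this stands: such an assessment can inform prospects, and the Discussion says that sustainability is addressed in planning, implementation and evaluation. But Phase III expressly says that data will be collected to assess sustainability, and the Discussion's remarks are the only indication the article gives of what the word means. Prospects are not the same as continuation.

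Several stronger readings are tempting and are not supported:

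- *That the 12 months are the funded period.* The article gives a deployment length and no funding period.
- *That the study team alone delivers the care.* The term is not defined, state personnel are trained as well, and the Strengths section aims to enable community health workers to provide home-based care.
- *That the electronic record has no field for who delivered care.* Phase III lists its contents only as examples, and an article may leave such detail to the full protocol.
- *That a given proportion of activity would be lost when the project ends.* The article gives no share for either workforce, and any assumed share would merely return itself as the loss.
- *That the quality-of-life, symptom or service results are wrong on this account.* They are unaffected.

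There is also a fair objection to the remedy. A share delivered by state workers while the project still trains and supervises them is itself observed under project support, and a model could show a high share and still fail later. That is right, and it limits how the share may be described.

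**Conclusion.** The point holds in a limited form. The 12-month data can support feasibility under project support and a judgement on prospects for sustainability. They cannot support sustainability as continuation after funding and the project end, because the article describes no observation in that period. The size is qualitative: one of the two attributes in the primary outcome lacks an observation that could establish it, and no estimate changes.

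The conclusion rests on two readings: that the Discussion's use of the word is the intended one, and that the assessment in Phase III is the only one planned after deployment. If the full protocol contains an assessment after the team withdraws, the point falls away. The conflict is among things the article itself states (outcome, timing, delivery and meaning) and does not depend on detail left elsewhere. It should be put right before results are reported, but it does not prevent the study from running.

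**What to change.** 1. Restate the primary outcome in Table 1 and the corresponding aim in Phase III as a model that is feasible under project support, with potential for sustainability.
2. In the electronic record already planned, enter for each palliative care contact and each referral whether it was delivered by project staff or by state health workers without them. If the record already holds this, say so.
3. Report the share delivered by state health workers over the deployment, for example by quarter, in one descriptive table. Label it an indicator of potential for sustainability, not proof of it.

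The cost is a wording change, a table and a small amount of data entry. The data entry is somewhat more if contacts are not yet logged one by one. The main downside is a less favourable primary claim.

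Collecting service data after the study team has withdrawn would be needed to claim sustainability in the Discussion's sense. That is an additional study period with its own cost and is not part of this change.
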